## Abstract

**Background:**

Due to limited resources, waiting periods for psychotherapy are often long and burdening for those in need of treatment and the health care system. In order to bridge the gap between initial contact and the beginning of psychotherapy, web-based interventions can be applied. The implementation of a web-based depression intervention during waiting periods has the potential to reduce depressive symptoms and enhance well-being in depressive individuals waiting for psychotherapy.

**Methods:**

In a two-arm randomized controlled trial, effectiveness and acceptance of a guided web-based intervention for depressive individuals on a waitlist for psychotherapy are evaluated. Participants are recruited in several German outpatient clinics. All those contacting the outpatient clinics with the wish to enter psychotherapy receive study information and a depression screening. Those adults (age ≥ 18) with depressive symptoms above cut-off (CES-D scale > 22) and internet access are randomized to either intervention condition (treatment as usual and immediate access to the web-based intervention) or waiting control condition (treatment as usual and delayed access to the web-based intervention). At three points of assessment (baseline, post-treatment, 3-months-follow-up) depressive symptoms and secondary outcomes, such as quality of life, attitudes towards psychotherapy and web-based interventions and adverse events are assessed. Additionally, participants’ acceptance of the web-based intervention is evaluated, using measures of intervention adherence and satisfaction.

**Discussion:**

This study investigates a relevant setting for the implementation of web-based interventions, potentially improving the provision of psychological health care. The results of this study contribute to the evaluation of innovative and resource-preserving health care models for outpatient psychological treatment.

**Trial registration:**

This trial has been registered on 13 February 2017 in the German clinical trials register (DRKS); registration number DRKS00010282.

**Electronic supplementary material:**

The online version of this article (10.1186/s13063-018-2657-9) contains supplementary material, which is available to authorized users.

## Background

Psychotherapy usually is a restricted resource, often associated with prolonged waiting periods for people seeking psychotherapeutic treatment. In Germany, on average, the waiting time to start psychotherapy is 4.5 months [1], with rural areas being particularly undersupplied [2]. These waiting periods are disadvantageous for people seeking help as well as the health care system. Individuals in need of mental health care experience an increased risk of chronification [3] and they are more dissatisfied with the help they receive [4]. They utilize more unspecific health care offers [5], causing high direct and indirect costs for the health care system [6]. Moreover, waiting periods contribute to people not starting psychotherapeutic treatment [7, 8] or not considering psychotherapy in the first place [9]. In order to address this issue, appropriate interventions should be offered to those unable to receive immediate psychotherapy.

One possibility to produce relief for people waiting for psychotherapy is the implementation of web-based self-help interventions. Web-based interventions have the potential to bridge treatment gaps [10, 11], as they can be applied flexibly, with comparably little time, space, and personnel resources [12, 13]. Since the late 1990s, a large body of research has emerged, confirming that web-based interventions are effective in reducing a range of psychological symptoms [14–18]. Particularly guided interventions offering feedback to participants have put forth promising effects [19]. Most recent research suggests that web-based interventions can be comparably effective to face-to-face psychotherapy [20]. While the efficacy of web-based interventions has been shown in various trials [21–24], the implementation of web-based interventions into health care systems worldwide is still in its infancy. One possibility to integrate web-based interventions into the health care system is their implementation during waiting periods. Offering web-based interventions to those waiting for psychotherapy may prove to be superior to mere waiting for several reasons: Individuals unable to enter psychotherapy could receive immediate access to an evidence-based intervention, therefore be provided with instant help; they could access the intervention 24 h a day, and use it in a familiar environment without time or travel costs [25]. For those in need of further treatment, interventions during waiting periods may facilitate progress in the subsequent face-to-face psychotherapy [26]. Hence, the implementation of a web-based intervention during waiting periods may prove to be particularly beneficial for both, help-seeking people and the adequate allocation of resources in our health care systems.

In order to assess the potential benefits of web-based interventions, they must be implemented in populations in need of help. One common complaint during waiting periods is depressive symptomatology [5]. With a point prevalence of about 8%, depressive symptoms are widespread in Germany [27], substantially reducing the quality of life of those affected [28, 29]. As almost half the patients in German outpatient clinics present with a depressive disorder [30, 31] and depressive symptoms often occur comorbid with other mental disorders [32], an intervention targeting the reduction of depressive symptoms is likely to be beneficial for many individuals waiting for psychotherapy.

The efficacy of web-based interventions for the reduction of depressive symptoms has been shown in several trials [22, 33]. However, there is limited evidence for their effectiveness and acceptance when implemented during waiting periods. To the best of our knowledge, three studies have examined web-based depression interventions during waiting periods [34–36]. Two studies reported intervention take-up rates between 26 and 53% [34, 37], high satisfaction among users [34] and large pre-post effect sizes of *d* = .75 [36]. The only randomized controlled trial testing a web-based depression intervention against mere waiting (treatment as usual) implemented an unguided intervention and had a number of methodological limitations, such as baseline assessment after randomization, substantial study dropout combined with missing intention-to-treat analyses and including participants without depressive symptoms [35]. At this point, no conclusions concerning the effectiveness of guided web-based depression interventions compared to treatment as usual during waiting periods can be drawn. Also, considering the results on intervention take-up and user satisfaction, findings concerning the acceptance of web-based interventions during waiting periods are quite heterogeneous and vary depending on the measure of acceptance (e.g., uptake vs. satisfaction rates) [34–36].

Taken together, the former studies highlight some of the challenges, such as low take-up rates [37], as well as the potentials of web-based interventions in this setting, such as high satisfaction among users [34] and possible reductions of depressive symptoms [36]. More research is needed to determine to what extent web-based interventions during waiting periods are superior to treatment as usual and which participant and intervention characteristics might impact on effectiveness and acceptance.

## Aims and research questions

The study aims at evaluating the effectiveness and acceptance of a guided web-based intervention for depressive individuals on a waitlist for outpatient psychotherapy. The following research questions are addressed:(Ia) Does the implementation of the web-based intervention have an effect on depressive symptoms when compared to waiting for psychotherapy without a web-based intervention? (effectiveness)(Ib) Does the implementation of the web-based intervention have an effect on other psychological symptoms, quality of life, and attitudes towards face-to-face psychotherapy and towards web-based interventions? (effectiveness)(II) How are intervention adherence (take-up rates, number of modules completed) and intervention satisfaction among depressive individuals waiting for face-to-face psychotherapy? (acceptance)(III) Which variables influence the effectiveness and acceptance of the web-based intervention (e.g., internet affinity, former psychotherapy)?

## Methods

### Design

A two-arm randomized controlled trial (RCT) of parallel design is conducted in order to investigate the research questions. Participants are randomized either to the intervention group receiving immediate access to the web-based intervention, or the waiting control group receiving treatment as usual (TAU) until follow-up assessment, and subsequently access to the web-based intervention. TAU in the control condition means waiting for face-to-face psychotherapy while having access to all other services of health care (e.g., general practitioner). Assessments take place before randomization (T1), seven weeks after randomization (T2), and at 3-months follow-up (T3). Figure 1 displays the flow of participants following the SPIRIT guidelines [38]. Figure 2 and Additional file 1 are available online. All procedures have been approved by the ethics committee of the Albert-Ludwigs-University Freiburg (approval number 404/16). The trial is registered in the German clinical trials register under DRKS00010282. We conduct and report the trial in accordance with the CONSORT 2010 Statement [39], the supplement of the CONSORT statement for pragmatic effectiveness trials [40] and the guidelines for executing and reporting internet intervention research [41].

**Fig. 1 Fig1:**
[figure not shown]
Study flow. *CES-D* Center for Epidemiologic Studies Depression Scale, *TAU* Treatment as usual

**Fig. 2 Fig2:**
[figure not shown]
SPIRIT-figure

### Recruitment

Participants are recruited at several psychotherapeutic outpatient clinics in Germany. All cooperating outpatient clinics have a current wait of at least two months before individuals enter psychotherapy. Consecutively, all those accepted onto the waitlist of an outpatient clinic are informed about the ongoing study and receive study information and screening material. All individuals on the existing waitlists with a remaining waiting time of at least two months are also invited to fill in screening material. Screeners are sent back directly to the research team. Respondents are tested for eligibility to participate in the study (cf. inclusion criteria). Eligible respondents receive an e-mail providing further study information and a link to the digital informed consent sheet. All respondents giving their informed consent are enrolled in the online baseline assessment (T1) and then randomized either to the intervention group (IG) or the control group (CG). Participants of the IG are provided with a link to access the web-based intervention. Participants of the CG are given the opportunity to access the web-based intervention without guidance after follow-up assessment. Recruitment has started in February 2017 and is ongoing until both treatment arms have reached a size of *n* = 68. All procedures were specified prior to recruitment start and are conducted as explicated in the clinical registration form (DRKS00010282).

### Inclusion and exclusion criteria

Individuals waiting for psychotherapy in one of the cooperating outpatient clinics and interested in study participation are eligible when they indicate (1) an age of 18 years and over, (2) working internet access, and (3) depressive symptoms (CES-D score > 22; Center for Epidemiologic Studies Depression Scale [42]). Exclusion criteria are reduced to a minimum. This procedure allows for high external validity as it leads to a heterogeneous sample of people seeking outpatient psychotherapy independent of a particular diagnosis. It allows individuals with other primary diagnoses (e.g. anxiety disorder) to participate in the study, as long as they show substantial depressive symptoms. Comorbid psychological symptoms are detected with the Brief Symptom Inventory (BSI; [43]). As additional criterion, participants must (4) submit their informed consent, (5) complete baseline assessments and (6) state no suicidal ideation on the BSI item no. 9 (score < 2). In case of a BSI item score of 1, participants must agree to a non-suicide-contract before entering the study. In case of suicidal ideation throughout the study, we follow a firm suicide protocol, which has been approved by the ethics committee. Potential steps in case of suicidal ideation include information on further help, non-suicide contracts, and telephone calls by a licensed psychotherapist.

### Randomization and blinding

An independent researcher of the Methodological Support Centre of the Rehabilitation Research Network Freiburg, who is not elsewhere involved in the study, prepared randomization and allocation of participants in advance. As a means of randomization, an automated computer-based system is implemented (https://www.sealedenvelope.com/) using permuted block randomization with variable block sizes of 4, 6, and 8 (randomly arranged), in a ratio of 1:1. Randomization is stratified by outpatient clinic. The means for blinding in this study are limited. Still, data analysts will be blinded by creating syntaxes before adding the treatment condition variable to the data set.

### Proposed sample size

The sample size calculation is based on the difference in change in the primary outcome (depressive symptoms) from pre- to post-treatment in both treatment arms (intention-to-treat analysis). Considering recent meta-analytic effect sizes for web-based depression interventions, an effect size of *d* = 0.56 [33] can be expected and is considered feasible for the type of intervention (guided intervention, naturalistic study design, cf. [44]). On the basis of a two-sample t-test at a two-sided significance level of .05, the study is planned to detect this effect with 90% power. This requires a sample of 68 individuals in each arm.

With a target sample size of *N* = 136 for randomization, at least 597 screeners have to be sent out. Based on previous research, it is expected that about 50% of the contacted people are interested in study participation [37]. Further, about 65% of those interested are expected to score above the cut-off for depressive symptoms [45], resulting in 194 potential participants. A 30% loss is expected due to incomplete baseline, suicidal ideation or missing informed consent, leaving 136 participants for randomization.

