When it comes to web-based interventions, considerable dropout rates have been reported [76]. The participants dropping out of the intervention will be asked for their reasons to do so, thus dropouts will be used for a deeper understanding of intervention acceptance and applicability. In an attempt to minimize intervention dropouts, we implement a web-based intervention with guidance [19]. Additionally, per protocol analysis will be performed for a high quality data analysis. Another limitation is that the main outcome data is based on self-reports. This is a frequently conducted approach with a favorable study cost–validity balance, still clinician-rated outcome measures would be beneficial. We have selected measures with high internal consistency and validity. In line with other research in the field (e.g., [63, 77]), retest-reliabilities are not reported as studies vary greatly in terms of evaluation times and sample characteristics, which makes retest-reliabilities difficult to interpret in the context of this study design. Also, due to related effort, no analyses of cost-effectiveness are performed in this study. Last, the recruitment of participants has started in February 2017; however, the study has been registered before the beginning of recruitment and no changes have been made to the registry.

The results of this study will be of great relevance for daily clinical practice, as they reflect the applicability of an evidence-based self-help treatment option for individuals seeking psychotherapeutic treatment. Addressing the problem of prolonged waiting periods, it is essential to investigate which treatment options are effective and accepted by those in need. Evidence-based interventions with minimal effort for outpatient clinics are scarce and urgently needed. Thus, implementing a web-based intervention in this setting may be beneficial for those on a waitlist and health care providers. Also, this study investigates a model to viably integrate web-based interventions into the health care system. Considering the growing interest and realization of new treatment approaches, such as stepped-care models [78, 79], web-based interventions have the potential to play an important role as low-intensity interventions in the treatment of depression [80]. As Kazdin and Blase [81] emphasize, innovative treatment approaches are needed to decrease the burden of mental diseases on a large scale.

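### The stated 90% power needs 68 observed T2 CES-D scores per arm, but 68 per arm is also the number randomised, so nothing is allowed for missing T2 scores

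*Protocol article*

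**What the plan says.** Under Proposed sample size, the calculation concerns the between-arm difference in CES-D change from pre- to post-treatment. It is labelled intention-to-treat. The inputs are:

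- effect: "an effect size of *d* = 0.56 [33] can be expected"
- test: "On the basis of a two-sample t-test at a two-sided significance level of .05"
- result: "the study is planned to detect this effect with 90% power. This requires a sample of 68 individuals in each arm"

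The next paragraph takes the same total, 136, as the target for randomisation and works back to 597 screeners. The only attrition it contains is this: "A 30% loss is expected due to incomplete baseline, suicidal ideation or missing informed consent, leaving 136 participants for randomization".

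Under Recruitment, enrolment continues until each arm has reached 68. Under Effectiveness analyses, all randomised participants enter a linear mixed model with group, time (three assessments) and their interaction, and data are assumed missing at random. The Background lists, among the limitations of the only earlier randomised comparison with mere waiting in this setting, "substantial study dropout combined with missing intention-to-treat analyses". That trial tested an unguided intervention.

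**The concern.** The number of outcomes needed for analysis is being used as the number to randomise. Loss is budgeted at each step up to randomisation and none after it. The 30% figure is easily mistaken for a dropout allowance, but its listed causes (incomplete baseline, suicidal ideation, missing consent) all act before a participant is allocated.

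The plan does expect some missing outcomes. It invokes missing at random, and it defines a per protocol set restricted to people with all three assessments. The power statement assumes there are none. At stake is how the result is read: a non-significant finding would be judged against a 90% figure that the stated calculation supports only with complete T2 data.

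**Working it through.** **Inputs.** From Proposed sample size: d = 0.56, two-sided alpha 0.05, power 90%, 68 per arm. From Randomization and blinding: 1:1 allocation. T2 loss: not given in the document; 10, 20 and 30% per arm are assumed here, equal in both arms.

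**1. Reproduce the plan's figure.** Normal approximation: n per arm = 2(1.960 + 1.282)² / 0.56² = 67.01, rounded up to 68.

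Exact two-sample t-test with n per arm: df = 2n − 2, noncentrality = d·√(n/2), and power is the probability that a noncentral t exceeds the two-sided 5% critical value.

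- n = 68: df = 134, noncentrality 0.56·√34 = 3.265, critical value 1.978, power 90.01%.
- n = 67: df = 132, noncentrality 0.56·√33.5 = 3.241, power 89.57%.

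So 68 is correct, and it is the bare minimum. One missing score per arm already takes the t-test below 90%.

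**2. Locate the 30%.** 597 × 0.50 = 298.5; × 0.65 = 194; × 0.70 = 136. The chain ends at randomisation. No factor follows it.

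**3. Power of the stated t-test after T2 loss.** Analysable n per arm = 68 × (1 − loss). The last column solves the same equation for d at 90% power.

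| Assumed T2 loss per arm | Analysable n per arm | Noncentrality at d = 0.56 | Power | d detectable with 90% power |
|---|---|---|---|---|
| 0% | 68 | 3.265 | 90.0% | 0.56 |
| 10% | 61.2 | 3.098 | 86.7% | 0.59 |
| 20% | 54.4 | 2.921 | 82.5% | 0.63 |
| 30% | 47.6 | 2.732 | 77.1% | 0.67 |

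Power reaches 80% at about 25% loss (n = 51, power 79.97%).

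**4. What baseline adjustment could recover.** This step needs two assumptions that are not in the document: that d = 0.56 is scaled to the SD of the post-treatment score, and a pre-post correlation ρ. Adjusting for baseline then gives an effective d of 0.56/√(1 − ρ²), which is 0.587 for ρ = 0.3 and 0.647 for ρ = 0.5. Using these in the formula of step 1:

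| Assumed T2 loss per arm | ρ = 0.3 | ρ = 0.5 |
|---|---|---|
| 10% | 89.6% | 94.4% |
| 20% | 85.9% | 91.7% |
| 30% | 80.9% | 87.7% |

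The recovery is real, but its size depends on ρ.

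**The case against.** **The analysis is a mixed model, not a t-test.** It keeps all randomised participants and uses the T1 and T3 scores, so it may have more power than the t-test suggests. This stands in part. With ρ = 0.5, step 4 gives about 92% at 20% loss, so a reader who inferred that the trial cannot reach 90% under any analysis would go too far. But the article does not rest its 90% on that model and gives no correlation. Neither the intention-to-treat label nor missing at random supplies T2 scores that were not observed.

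**A reader might also infer that the mixed model takes nothing from baseline,** because clinic is the only random effect named. The document does not support that. It is silent on the covariance between a person's repeated scores, a detail that a condensed article may leave to the full analysis plan.

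**The evidence for missing T2 scores is thin.** This is fair. The Discussion remark that "considerable dropout rates have been reported" is tempting support, but the sentences around it concern leaving the intervention, which the article defines by modules completed. A non-completer can still answer the T2 questionnaire, so the remark is not evidence of missing T2 scores. The Background statement does concern study dropout, but in one trial of an unguided programme, whereas this one is guided. Neither statement gives a rate.

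**Nothing is miscalculated.** Correct: 68 and 136 both reproduce. The fault is an unstated assumption of complete T2 data.

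**Conclusion.** The point holds for the calculation that the article states. The 90% is the power with 68 observed T2 scores per arm, and the design randomises exactly 68 per arm with no allowance for loss. On that t-test, power is about 87, 82 and 77% at assumed T2 losses of 10, 20 and 30% per arm. It stays at about 80% or above up to roughly 25% loss.

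The size rests entirely on the assumed loss, because the document gives none. It applies to the t-test basis and not to every analysis that the trial might run. Missing scores at this level reduce precision; the sample-size shortfall itself does not affect the type I error. This should be fixed as a matter of stating the power correctly. It is not a flaw that invalidates the design.

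**What to change.** In Proposed sample size, state that 68 per arm is the number of analysable T2 scores required for 90% power, state an assumed T2 loss, and give the power at that loss. Possible wording: *68 per arm gives 90% power if all T2 assessments are obtained, about 82% if 20% are missing and about 77% if 30% are missing.* Make clear that the 30% in the recruitment chain precedes randomisation.

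Optionally, base the power statement on a baseline-adjusted analysis. The pre-post correlation must then be given as an assumption with a range, for example 0.3 to 0.5, giving about 86 to 92% at 20% loss and about 81 to 88% at 30% loss. The scale of d (post-treatment score or change score) should be stated with it. A single correlation of 0.5 would only replace one unsupported figure with another.

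The cost is a few sentences and a somewhat less favourable headline figure. No further enrolment is needed to correct the statement.
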